### Procedure for unblinding if needed {17b}

If a serious adverse event occurs, the participant’s allocation will be unblinded. The incident will be promptly reported to the Ethics Committee.

## Data collection and management

### Plans for assessment and collection of outcomes {18a}

Licensed therapists with at least 3 years of experience will conduct biofeedback treatment for both the intervention and control group patients. Acupuncturists conducting PEPNS for the intervention group will have a minimum of 2 years of acupuncture practice. A 2-day training session led by senior research team members will prepare therapists, acupuncturists, and assessors on all aspects of the study from diagnosis to data collection. Inspectors at each center will monitor patient enrollment, treatments, and data quality.

### Plans to promote participant retention and complete follow-up {18b}

Strategies to enhance participant retention and ensure completion of follow-up: Following each week of treatment, patients will be automatically scheduled for their next session. Additionally, patients will receive a weekly reminder via SMS on their mobile phones regarding their upcoming treatment appointment.

### Data management {19}

Data will be recorded on paper and entered into a secure electric data management system (developed by an independent data management agency, Linkermed Technology, Beijing, China) for error checks. All records will be stored safely for at least 10 years after the study while ensuring patient privacy. Personal data will be kept separate from the analysis. Both the intervention and control groups will be assigned anonymous numerical codes (1, 2) to blind the individual conducting the statistical analysis. The collected data will only be used for this research.

### Confidentiality {27}

Personal information will be retained solely by the therapist within a secure electronic data management system. All records will be securely stored for at least 10 years after the study to safeguard patient privacy.

### Plans for collection, laboratory evaluation, and storage of biological specimens for genetic or molecular analysis in this trial/future use {33}

Not applicable, no samples were collected.

## Statistical analysis

### Statistical analysis plan (SAP) for primary and secondary outcomes {20a}

#### Overview

The primary and secondary outcome analyses will be conducted using IBM SPSS Statistics version 27.0. A comprehensive SAP has been established to ensure robust and accurate interpretation of the data. This plan adheres to the guidelines published in JAMA [24] and incorporates principles for the prospective reporting of statistical analysis plans for RCTs [25].

#### Data processing and preliminary steps

Normality test: Data will be assessed for normality using the Shapiro-Wilk test.Handling baseline imbalances: If baseline characteristics and outcome measures show imbalances, analysis of covariance (ANCOVA) will be applied to adjust for these differences.Data presentation: Normally distributed continuous variables will be presented as means ± standard deviations (SD). Non-normally distributed or ordinal variables will be presented as medians with interquartile ranges (IQR). Categorical variables will be presented as counts and proportions.Missing data: The last observation carried forward (LOCF) method will be used to handle missing data points. Other rules are referenced in Item 20c.

#### Primary outcome analysis

The primary outcome of this study is the change in LARS scores.Descriptive statistics: continuous variables (normally distributed): means ± SD. Continuous variables (non-normally distributed): medians with IQR. Categorical variables: Counts and proportions.Inferential statistics: Student’s *t*-test: used for analyzing normally distributed primary outcome measures (LARS scores). Paired* t*-tests: to compare pre-treatment and post-treatment improvement rates within each patient for LARS scores. Independent sample *t*-tests: to compare improvement rates in LARS scores between the intervention and control groups. Mann-Whitney *U* test: For inter-group comparisons of non-normally distributed LARS score data. Wilcoxon signed-rank test: to compare pre-treatment and post-treatment improvement rates in LARS scores for non-normally distributed data within each patient. Intergroup rank sum test: To assess inter-group differences in ordinal data.

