**Methods and analysis:**

In this two-armed multicenter RCT, 242 participants with LARS after rectal surgery will be randomly assigned to undergo B-PEPNS (intervention group) or biofeedback (control group). Over 4 weeks, each participant will undergo 20 treatment sessions. The primary outcome will be the LARS score. The secondary outcomes will be anorectal manometry and pelvic floor muscle electromyography findings and the European Organization for the Research and Treatment of Cancer Quality of Life Questionnaire-Colorectal 29 (EORTC QLQ-CR29) scores. Data will be collected at baseline, post-intervention (1 month), and follow-up (6 months).

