#### Primary outcome

The primary outcome will be defined as the improvement rate. This will be determined by assessing the change in the LARS scores for each patient. The improvement rate will be calculated as follows:

Improvement rate (%) = [(LARS score before treatment − LARS score after treatment) ÷ total score before treatment] × 100

The treatment will be considered effective if the improvement rate surpasses 25%.

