### Sample size {14}

Based on a prior study [10] involving 45 patients in each group (efficacy rate, 65.6%:46.7%), the required sample size for this study was computed utilizing the Power Analysis and Sample Size 15 software (NCSS Statistical Software, UT, USA). A sample size of 210 patients was determined to achieve a power (1-beta) of 0.80 and an alpha (significance level) of 0.05, with group allocation in a 1:1 ratio. Factoring in potential dropouts (15% of the participants), the total sample size was adjusted to 242 in total (*n* = 121 in each group).

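### The sample size is for a difference in responder proportions, but the primary analysis lists only t-tests and rank tests, so the stated 80% power belongs to a different analysis from the planned one

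*Protocol article*

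**What the plan says.** Four places in the protocol article bear on the primary outcome.

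- **Abstract, Methods and analysis:** "The primary outcome will be the LARS score".
- **Outcome {12}, Primary outcome:** "The primary outcome will be defined as the improvement rate". The formula is the pre-treatment score minus the post-treatment score, divided by the pre-treatment score, times 100. A binary rule follows, in per cent: "The treatment will be considered effective if the improvement rate surpasses 25".
- **Sample size {14}:** the only effect input comes from a prior study "involving 45 patients in each group (efficacy rate, 65.6%:46.7" per cent). The result is 210 patients for power 0.80 and alpha 0.05, raised to 242 for dropout.
- **Statistical analysis {20a}, Primary outcome analysis:** "The primary outcome of this study is the change in LARS scores". Between the arms, independent-samples t-tests are planned "to compare improvement rates in LARS scores between the intervention and control groups", and the Mann-Whitney test "For inter-group comparisons of non-normally distributed LARS score data". A rank-sum test is listed for ordinal data. Within patients, paired t-tests are planned "to compare pre-treatment and post-treatment improvement rates within each patient for LARS scores", with the Wilcoxon signed-rank test as the non-normal counterpart.

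Chi-square and Fisher's exact tests for categorical data are named only under Secondary outcome analysis. Outcome {12} schedules assessments at baseline, 1 month and 6 months and does not say which follow-up visit is primary.

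**The concern.** A sample size calculation supports one hypothesis, tested in one way on one variable. Here the variable that was sized is whether a patient is a responder, while the variables that are tested are the percentage improvement or the score itself, by means or ranks. The power statement therefore does not carry over to the planned analysis, and the analysis it does describe is not listed for the primary outcome.

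Two further consequences follow. First, responder status, percentage improvement and change in score can give different answers in the same data, and there are two follow-up visits. With each p-value judged at 0.05 and no single primary fixed, the version that favours treatment could be chosen after the results are known. Second, the paired tests cannot be carried out as worded. The improvement rate already uses both the before and the after score, so a pre-treatment improvement rate does not exist.

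**Working it through.** **1. Reproduce the plan's figure.** Inputs from Sample size {14}: p1 = 0.656, p2 = 0.467, alpha 0.05, power 0.80, 1:1 allocation. Two-sided testing is taken from Secondary outcome analysis, where p-values are stated to be two-tailed.

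Unpooled two-proportion formula:

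n per arm = (1.960 + 0.8416)² × [p1(1 − p1) + p2(1 − p2)] / (p1 − p2)²

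= 7.849 × (0.2257 + 0.2489) / 0.189²

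= 7.849 × 0.4746 / 0.03572 = 104.3, so 105 per arm and **210 in total**.

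This matches the stated figure exactly. The pooled-variance version gives 107.01, so 108 per arm and 216; the arcsine version gives 214. At 105 per arm the pooled z-test has 79.2% power. The calculation is one for proportions. No mean difference or standard deviation for the LARS score, its change or the improvement rate appears in the document.

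**2. Set this against the planned primary test.**

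| Section | Variable | Type | Test |
|---|---|---|---|
| Outcome {12} | Percentage improvement | Continuous | – |
| Outcome {12} | Improvement above 25% | Binary | – |
| Sample size {14} | Efficacy rate | Binary | Two proportions (by reproduction) |
| Primary outcome analysis | Change in LARS score; improvement rate; LARS score | Continuous or ranked | t-test, Mann-Whitney |
| Secondary outcome analysis | Categorical data | Categorical | Chi-square, Fisher |

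**3. What power does the planned t-test have?** The document does not fix it. With n = 105 per arm and two-sided 0.05, power ≈ Φ(d√(n/2) − 1.96), where d is the standardised mean difference (SMD) and √(105/2) = 7.246.

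| Assumed SMD | Power |
|---|---|
| 0.20 | 30.5% |
| 0.25 | 44.1% |
| 0.30 | 58.5% |
| 0.35 | 71.8% |
| 0.387 | 80.1% |
| 0.40 | 82.6% |
| 0.50 | 95.2% |

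The two efficacy rates convert to an SMD only under three assumptions: improvement is normal, the SDs are equal, and the prior study's efficacy rate used the same 25% cut-off. Then d = z(0.656) − z(0.467) = 0.4016 + 0.0828 = 0.484, and power is about 94% for the t-test and about 93% for Mann-Whitney (relative efficiency 0.955). The third assumption has no support in Sample size {14}.

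**4. Room for selection.** As an illustration, take two candidate primaries, each tested at two-sided 0.05 under the null, with the smaller p-value reported. The chance of at least one significant result is 7.0% at correlation 0.9, 7.8% at 0.8 and 8.8% at 0.6. The correlations are assumed.

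**5. The paired tests.** By the formula in Outcome {12}, each patient has one improvement rate per follow-up visit, and none before treatment. There is no pre/post pair of rates to compare.

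**The case against.** The strongest reply is that the conflict is smaller than it looks. The abstract names the instrument, as abstracts do. Outcome {12} says the improvement rate is derived from the change in LARS scores, so the analysis section's change in LARS scores may be shorthand, and its independent t-test does name improvement rates. This largely stands: the differing labels are not by themselves four separate definitions. What remains is a continuous improvement measure on one side and a responder proportion on the other, with some added ambiguity because the Mann-Whitney line refers to LARS score data.

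It can also be said that the chi-square line was meant for responders. The named secondary outcomes are measurements or scores, the paragraph that holds it also carries trial-wide rules, and counts and proportions are listed among the primary descriptive statistics. That is possible, but the text does not say so. The fair statement is that no test of proportions is assigned to the primary outcome. A separate analysis plan could choose among the versions but could not agree with all of them.

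A reader might infer that the trial is underpowered. The document does not support that: no SMD is given, and under the assumptions in the working the t-test would exceed 80% power. Nor does it support a firm 94%, which needs a cut-off the protocol does not attribute to the prior study. A reader might also infer that natural recovery, which the Discussion describes, will be credited to treatment through the within-arm tests. A between-arm comparison is planned as well, and nothing says efficacy will be concluded from the paired tests, so that risk is conditional.

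**Conclusion.** The point holds as a contradiction in the printed text. The 210 patients and the 80% power belong to a comparison of two proportions, while the tests listed for the primary outcome compare means or ranks. The reproduction is exact under the unpooled two-sided formula and needs no outside assumption.

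The size of the mismatch in power cannot be stated as one number: it runs from about 31% to 95% over SMDs of 0.20 to 0.50. The 7% to 9% type I error is an illustration for two tests with assumed correlations of 0.9 to 0.6, not an estimate for this trial. The paired tests of improvement rates are wrong as worded, which is a secondary matter. The main point should be settled before unblinding, because it decides what the trial's principal conclusion will be about.

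**What to change.** Before unblinding, name one primary variable, one time point (1 or 6 months) and one between-arm test, and state them identically in the abstract, Outcome {12}, Sample size {14} and Primary outcome analysis. The choice is the sponsor's; either route is sound.

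- **Responder primary:** the proportion with LARS improvement above 25%, compared by a two-proportion test or by logistic regression adjusted for baseline LARS score. This keeps the 210 calculation, approximately so for the adjusted model. The continuous score becomes a secondary outcome.
- **Continuous primary:** the LARS score at the chosen visit by ANCOVA adjusted for baseline, with the power in Sample size {14} restated from a stated mean difference and SD. Responder status becomes a secondary outcome.

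In both cases, remove the paired t-test and Wilcoxon signed-rank test of improvement rates, or reword them as descriptive within-arm comparisons of LARS scores that carry no efficacy conclusion.

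The cost is protocol and analysis plan wording and a registry update. No new data are needed.

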## Discussion

The management of LARS is crucial considering its high prevalence and severe impairment of the quality of life [26]. The treatment timing is important, and early intervention for LARS is preferred as it is better for neural functions [27]. Therefore, as per our protocol, our intervention can start 1 month postoperatively for anal preserve rectal cancer or temporary ileal stoma retraction.

Opting for a combined approach of biofeedback and PEPNS for treating LARS is grounded in their potential synergistic action in LARS management as well as their high operational feasibility. Biofeedback, utilizing superficial electrodes and anal internal sensing probes, accurately detects pelvic muscle movements, providing effective guidance to patients during pelvic floor exercises. It also promotes pelvic muscle rehabilitation through superficial electrical stimulation. On the other hand, PEPNS precisely locates the perineal nerve positions via percutaneous needling, directly stimulating these nerves to increase the resting sphincter pressure, thereby enhancing bowel control. Biofeedback is a routine outpatient procedure conducted in many tertiary hospitals, whereas PEPNS implementation only requires an acupuncture apparatus and basic training for physicians in needling techniques, which can be easily sought in Chinese medicine hospitals. Hence, the execution of this study is comparatively straightforward.

The symptoms of LARS tend to be more severe in the initial months after surgery, especially in the first 4 months, followed by a gradual improvement and stabilization between 6 months to 1 year [4, 5]. Therefore, our assessments not only include a short-term evaluation 1 month after treatment but also a long-term evaluation after 6 months. This is aimed at minimizing potential biases due to natural symptom variations over time. Additionally, based on the results from the 6-month long-term evaluation, we will determine the necessity for further assessment after 1 year.

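### The paired tests listed for the primary outcome compare a pre-treatment improvement rate that does not exist; read as pre v post LARS scores, they are within-arm tests that do not address superiority

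*Protocol article*

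**What the plan says.** Protocol article, Primary outcome: "The primary outcome will be defined as the improvement rate". Its formula takes "LARS score before treatment − LARS score after treatment", divides by the pre-treatment score and multiplies by 100.

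Protocol article, Primary outcome analysis: the section opens with "The primary outcome of this study is the change in LARS scores". Under inferential statistics it lists a paired t-test "to compare pre-treatment and post-treatment improvement rates within each patient for LARS scores" and a Wilcoxon signed-rank test "to compare pre-treatment and post-treatment improvement rates in LARS scores for non-normally distributed data within each patient". The same list has independent-sample t-tests "to compare improvement rates in LARS scores between the intervention and control groups", and Mann-Whitney tests for non-normal data. Nothing marks the paired tests as descriptive or supportive.

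Secondary outcome analysis carries the same methods over to manometry, EMG and QLQ-CR29, names paired t and signed-rank tests again, and sets a two-sided 5% significance level.

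Three other statements bear on the point. Trial design {8} calls this a superiority study. Explanation for the choice of comparators {6b} gives both arms the same biofeedback. The Discussion describes symptoms as worst in the first months after surgery, "followed by a gradual improvement and stabilization between 6 months to 1 year".

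**The concern.** There are two linked problems.

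The first is one of definition. An improvement rate is already a before-after contrast, so it cannot be split into a pre-treatment and a post-treatment value. Two of the tests named for the primary outcome have no first member of the pair.

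The second arises from the obvious repair. If the authors meant LARS scores before and after treatment, each test asks whether patients in one arm changed from baseline. (If both arms were pooled, which the text does not rule out, the test would be even further from the treatment question.) The trial asks whether adding PEPNS to biofeedback does better than biofeedback alone. A significant change within an arm mixes any PEPNS effect with the effect of biofeedback and with change over time since surgery. Listed as primary inference, such p-values leave room for a benefit to be read from both arms improving, or from one arm crossing 0.05 and the other not. Neither pattern is evidence of a difference between arms.

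**Working it through.** **Definition.** Let B be the score before treatment and A the score at a later visit. The article's rate is R = (B − A) ÷ B × 100. Assessments are at baseline, 1 month and 6 months, so each patient has one R at 1 month, one at 6 months, and none before treatment. The only way to force a baseline value is to set A = B, which gives R = 0 for everyone. The paired test then becomes a one-sample test of R against 0. This step needs no assumed figure.

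**Number per arm.** Sample size {14} gives 65.6% v 46.7%, power 0.80, alpha 0.05 (two-sided by the Secondary outcome analysis section), 1:1 allocation and 210 patients. The unpooled two-proportion formula reproduces this:

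n = (0.656 × 0.344 + 0.467 × 0.533) × (1.960 + 0.842)² ÷ (0.656 − 0.467)² = 0.4746 × 7.849 ÷ 0.03572 = 104.3, so 105 per arm and 210 in total.

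I use n = 105, with 121 (the number randomised per arm) as the alternative if every randomised patient is analysed with imputation.

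**Chance that a within-arm test is significant.** The article gives neither the size nor the SD of LARS change that occurs without PEPNS. Assume a standardised mean change dz (mean change ÷ SD of change) from 0.1 to 0.5, the same in both arms, so that PEPNS adds nothing. With the normal approximation,

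p = Φ(dz × √n − 1.96).

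For example, at n = 105 and dz = 0.1: Φ(1.025 − 1.960) = Φ(−0.935) = 0.175. With independent arms, both are significant with probability p² and exactly one with probability 2p(1 − p).

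| Assumed dz | p, n = 105 | p, n = 121 | Both arms, n = 105 | Exactly one arm, n = 105 |
|---|---|---|---|---|
| 0.1 | 0.175 | 0.195 | 0.03 | 0.29 |
| 0.2 | 0.536 | 0.595 | 0.29 | 0.50 |
| 0.3 | 0.867 | 0.910 | 0.75 | 0.23 |
| 0.4 | 0.984 | 0.993 | 0.97 | 0.03 |
| 0.5 | 0.999 | 1.000 | 1.00 | 0.002 |

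A dz of 0.27 (n = 105) or 0.25 (n = 121) gives 80% power within an arm.

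The two misleading patterns do not peak together. One arm significant alone is most likely near dz = 0.2, and both arms significant dominates from about 0.3 upwards.

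**The case against.** The strongest reply is that this is a slip of the pen. The section names change in LARS scores as the outcome, so the intended comparison is evidently score before against score after, which can be computed. The randomised comparison is also planned, by independent-sample t-test or Mann-Whitney test, and nowhere does the article say that efficacy will be claimed from within-arm p-values. This largely stands. The slip is probably one of wording, and the between-arm result does not depend on it. It remains true that the phrase appears twice, for both paired tests, in the list of primary inferential methods, and that correcting the wording still leaves within-arm tests there without a label.

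A reader might go further and infer that these tests are bound to be significant from natural recovery alone. The documents do not support that:

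- They give no size or SD of natural change, and the probability runs from about 17% to 99.9% over the range above.
- Both arms receive active biofeedback, so a within-arm change could not be put down to natural recovery alone.
- The inclusion criteria set a minimum of 1 month of dysfunction after surgery but no upper limit, so some patients may be past the recovery period. The Background adds that symptoms often persist.

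A single figure for one arm being significant alone would also mislead, since it moves between about 0.2% and 50% across the table.

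The Discussion says the 6-month assessment is meant to reduce bias from natural variation. A later visit does not do that for a within-arm test; only the comparison with the concurrent control does.

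**Conclusion.** The point holds in two parts of different strength. It is certain, from the article's own formula, that no pre-treatment improvement rate exists and that the paired t-test and signed-rank test are undefined as written. Read instead as tests of LARS score, they can reach significance without any PEPNS effect and do not address superiority. That follows from the design, but its frequency does not: it rests on an assumed dz, equal change in both arms, and about 105 analysed per arm. The trial keeps a valid between-arm comparison, so this is a correction that should be made to the stated analysis, not a flaw that undermines the trial. For the secondary outcomes only the second part applies, because that list does not repeat the undefined rate.

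**What to change.** In Primary outcome analysis, either remove the paired t-test and the Wilcoxon signed-rank test from the inferential methods, or restate them as a descriptive summary: within-arm change in LARS score from baseline at each visit (mean or median) with a 95% confidence interval. Treat the paired and signed-rank entries in Secondary outcome analysis in the same way. Add one sentence saying that every conclusion about efficacy rests on the between-arm comparison already planned.

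The cost is a change of wording. No data, visits or patients are added, and the sample size is untouched. The only loss is the within-arm p-values.
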